### Interim analyses {21b}

Not applicable. Interim analyses will not be done in this study.

### Methods for additional analyses (e.g. subgroup analyses) {20b}

Depending on the course and outcomes of this study, additional sub-group analyses might be performed, e.g. between the different ASIA scores, how often someone has a PU, if someone has a PU during different times during the study, adherence to the intervention and the grade and location of the PU. The association between all risk factors and PU development/ incidence will also be looked at.

### Plans to give access to the full protocol, participant level-data and statistical code {31c}

Initially, the data will only be analysed for the purpose of this study. The data will then first become available for the involved researchers to identify other research purposes and kept for a maximum of 1 year. Subsequently, the research group intends to make the coded and de-identified syntaxes and data files accessible for further research and verification. However, access to the data set will be limited and access can only be allowed under certain conditions, because it will be hard to fully anonymize the dataset. If there are questions about the validity of the study results, the data may be made available to a requesting party with appropriate security measures. The party is only allowed to use the data to check the study results. The data of this study can only be reused for research in the same line as this study (similar goals, aims and purposes). Next to that, access to the data will only be granted when there is approval of the original research team and assurance that the receiving party will sufficiently protect the data. Extra safety precautions will be made when the data will leave the EU. The research group intend to share coded and de-identified syntaxes and data-files.

## Oversight and monitoring

### Composition of the coordinating centre and trial steering committee {5d}

This multicentre trial will be coordinated by researchers of the Vrije Universiteit Amsterdam together with researchers from the Amsterdam UMC and Reade. This trial will be directed by the principal investigator (TJ), coordinating investigator (SG) and by the executive researcher (BW). No overall steering committee will be involved in this study. All project members will play a part in the monitoring during the trial period and will meet weekly with a small group and every 3 months with all involved researchers.

### Composition of the data monitoring committee, its role and reporting structure {21a}

Because of the expected low risk of this study, a ‘Light Monitoring’ is chosen, hence without an additional monitoring committee. Since monitoring is outsourced in a lighter form, the task of monitoring will be exchanged with another study group that is independent during the monitoring or assessment.

### Adverse event reporting and harms {22}

All adverse events reported spontaneously by the participant or observed by the investigator or his staff will be recorded. The investigator will report all SAEs to the sponsor without undue delay after obtaining knowledge of the events. The sponsor will report the SAEs through the web portal toetsingonline.nl to the accredited METc that approved the protocol, in this case, Amsterdam UMC, location VUmc. The researcher will report the AE of SAE within the specified time as indicated. All AEs will be followed until they have abated, or until a stable situation has been reached. SAEs need to be reported until the end of the study within the Netherlands, as defined in the protocol.

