#### Intervention group

The intervention group will receive usual care plus ES. ES will be applied using a 4-channel portable stimulator (EMP 4 Eco+; Wuxi Jiajian Medical Instrument Co., Ltd; China) connected with surface electrodes, either self-adhesive electrodes or a custom-made lycra garment with built-in surface electrodes (Berkelbike BV, Sint-Michielsgestel, NL). The researchers decide who receives a garment or surface electrodes while looking at the following criteria; the participant’s choice, functionality, independence, the presence of wounds on the back and the presence of a stoma. ES will be given for at least 60 min bi-phasically with a 6 s:18 s activation-rest cycle, 50 Hz (frequency), a 300–400-μs pulse duration and the output current amplitude (mA) will be determined per participant. The current amplitude resulting in the best tetanic contraction without creating discomfort or excessive muscle contractions will be determined for each participant individually during the baseline measurement by the ES expert or research assistant. This amplitude will be used as starting point for the home stimulation, participants will be instructed to increase the mA if no activation or only twitches are visible. The activation within the activation-rest cycle consists of 2 s ramp-up, 3 s full activation and 1 s ramp-down followed by 18 s rest. The 6 s:18 s activation-rest cycle is based on the 1:6 cycle which has been proven to be effective and seems more effective than a cycle with less rest [34, 37]. The 1:6 cycle is multiplied by 3 to create a longer contraction and rest period, which might lead to a lower risk for long-term muscle fatigue. The researchers present it as a 6 s:18 s activation-rest cycle, since the ramp-up and down are also seen as activation.

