### Criteria for discontinuing or modifying allocated interventions {11b}

When one of the following adverse events or inconveniences occurs during ES, the intervention needs to be stopped temporarily:
Red, raised or itchy skin [38–40]Muscle pain [38, 40]Increase in nerve painFeeling uncomfortable [38, 40]Orthostatic hypotension: dizziness, light-headedness, blurred vision, palpitation or shortness of breath [38, 41]Autonomic dysreflexia, dysfunction or dysregulationPain induced by spasms

The adverse events mentioned above are temporary and usually disappear once the stimulation has stopped. If problems continue to arise during stimulation, the intervention will be stopped.

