#### Primary outcome

##### Pressure ulcer incidence

PU incidence in the sacral or ischial tuberosity’s region (in total and for each severity category according to the EPUAP [22]) will be recorded throughout the 12-month study period by the participant or his/her caregiver. Every 2 weeks, each participant will receive an email or notification with the question of whether a new PU has been identified or whether an existing PU is still present. If the answer is ‘yes’ then the following steps need to be taken:
A digital photo of the wound will be made by the participant or his/her caregiver according to standardized instructions and will be sent to a nurse practitioner specialized in wound care. All pictures will be analysed by the same well-trained and experienced nurse practitioner. The location of the wound and the severity (category 1–4) will be classified according to the EPUAP [22]. If there is a wound visible in the photo the wound is also evaluated with the TIME model, a method for evaluating local disruptive factors [21].Change in risk score will be evaluated with a modified CBO list, derived from the main elements of the Norton, Waterlow, Braden scale and 2 Dutch lists, i.e. PrePURSE and CBO list [1].(Possible) Cause of PU needs to be described by the participant.Healing tendency will be calculated by the experienced nurse practitioner by dividing the starting content (depth wound) or surface (superficial wound) by the number of days to complete wound healing. The outcome will be the average number of surface area reduction per day. This can only be done in case of a wound severity category 3 or 4 [42].

Each participant will be asked to take a standard photo of the sacral and ischial tuberosities regions every month. This picture should be taken regardless of a pressure ulcer is present.

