### Plans to promote participant retention and complete follow-up {18b}

Every 2 weeks, participants will get an invitation to fill in some questions regarding the PU incidence and the intervention group will also be asked to complete the diary. When opening the online questionnaire, an overview is visible showing which questionnaire has already been completed and which questionnaire has not yet been completed. When a questionnaire is not fully completed or submitted a week after the invitation, the local researcher of Reade will contact the participant.

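### Adverse events are collected passively although ES is self-applied at home, so transient non-skin reactions are likely to be under-recorded and recorded counts may not be comparable between arms

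*Protocol article*

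**What the plan says.** All references are to the protocol article.

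- **How harms are collected** (Adverse event reporting and harms {22}): "All adverse events reported spontaneously by the participant or observed by the investigator or his staff will be recorded". No section describes a structured adverse event question in either arm.
- **Where ES is given** (Intervention group): "This amplitude will be used as starting point for the home stimulation, participants will be instructed to increase the mA" when there is no activation or only twitching. The abstract gives the dose as four or more sessions a week of at least an hour, for one year.
- **Expected reactions** ({11b}): "When one of the following adverse events or inconveniences occurs during ES, the intervention needs to be stopped temporarily". Seven items follow: skin reaction, muscle pain, increased nerve pain, discomfort, orthostatic symptoms, autonomic dysreflexia and spasm pain. The section adds: "The adverse events mentioned above are temporary and usually disappear once the stimulation has stopped".
- **Scheduled physical measurements** (Secondary outcome measures): baseline and months 3, 6 and 12.
- **Regular contact with both arms** ({18b}): "Every 2 weeks, participants will get an invitation to fill in some questions regarding the PU incidence". The section on PU incidence describes the content: "each participant will receive an email or notification with the question of whether a new PU has been identified", or whether an existing one persists. It also asks every participant for a monthly photo of the sacral and ischial regions.
- **Contact in the ES arm**: a diary ({18b}), a usability questionnaire on the ES system at months 3, 6, 9 and 12 (Table 1), and local staff available for questions about ES ({17a}).
- **Oversight** ({21a}): "Because of the expected low risk of this study, a ‘Light Monitoring’ is chosen, hence without an additional monitoring committee".

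**The concern.** The collection method does not suit the intervention. Reactions would arise at home, mostly without staff present, and would usually be over before the next scheduled measurement. Whether they are recorded then depends largely on the participant raising them unprompted. The one instrument that reaches everybody every two weeks is described as asking about PUs only.

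Two things are at stake. First, a low count of, say, dysreflexia or orthostatic symptoms could mean that ES is well tolerated or that nobody asked. The expected low risk, which is the stated reason for light monitoring, would be only weakly tested by the trial's own data. The Discussion foresees wide implementation if ES works, so this matters beyond the trial. Second, several listed symptoms also occur in people with spinal cord injury who do not use ES. For these, an arm with more contact about its treatment has more occasions to mention a symptom, and a difference in recorded counts could reflect contact rather than ES.

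**Working it through.** The document states no adverse event rate and no capture rate, so there is no figure to reproduce. The check is mainly textual.

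**Step 1: which listed events have a solicited route?**

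| Event | Solicited in both arms? | Other possible route, ES arm |
|---|---|---|
| Skin reaction | Partly: fortnightly PU question, monthly photo of sacral and ischial regions | Diary, usability questionnaire, interviews |
| Muscle, nerve or spasm pain | None described | Same |
| Discomfort during ES | None described; no control counterpart | Same |
| Orthostatic symptoms | None described | Same |
| Autonomic dysreflexia | None described | Same |

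The gap lies mainly in the non-skin events. The diary's stated content is ES usage (Usability and user-friendliness), and the usability questionnaire includes open questions. These may surface reactions but are not described as adverse event counts.

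**Step 2: could observation by staff fill the gap?** A reaction that ends with the session is visible to staff only if it happens in their presence. Three scheduled follow-up measurements in a year give little scope for that. The abstract adds a month-9 assessment, which would not change this.

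**Step 3: where does comparability arise?** Reactions defined as occurring during ES have no control counterpart. The question applies only to events possible in either arm: spasm pain, nerve pain, orthostatic symptoms and dysreflexia. For these the ES arm has more reporting occasions.

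**Step 4: illustration of under-recording.** Inputs: n = 50 per arm (Sample size {14}); p = true 12-month risk of one event, assumed 5% or 10%; c = chance that an affected participant has it recorded, assumed 30%, 50% or 100%. Participants are taken as independent.

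Expected number recorded = 50 × p × c. Chance of none recorded = (1 − p × c)^50.

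| p | c | Expected recorded | Chance of none |
|---|---|---|---|
| 10% | 30% | 1.5 | 0.97^50 = 0.218 |
| 10% | 50% | 2.5 | 0.95^50 = 0.077 |
| 10% | 100% | 5.0 | 0.90^50 = 0.005 |
| 5% | 30% | 0.75 | 0.985^50 = 0.470 |
| 5% | 50% | 1.25 | 0.975^50 = 0.282 |
| 5% | 100% | 2.5 | 0.95^50 = 0.077 |

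**Step 5: illustration of unequal capture.** Take an assumed true risk of 20% in both arms, so 50 × 0.20 = 10 affected in each. Recorded risk ratio = c(ES) / c(control).

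- Capture 50% and 50%: 5 against 5, ratio 1.0. Both arms are under-counted but comparable.
- Capture 80% (ES) and 40% (control): 8 against 4, ratio 2.0 with no true difference.
- Capture 40% (ES) and 80% (control): 4 against 8, ratio 0.5.

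The last two lines show that the sign depends wholly on capture rates that the document does not give.

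**The case against.** The strongest reply is that no claim in the trial depends on this. Harms are not among the objectives or listed outcomes, and no between-arm safety comparison is described. Serious events are to be reported without delay. People with a history of severe autonomic dysreflexia are excluded. The process evaluation covers unintended outcomes, draws on a question in the ES questionnaire and diary, and includes interviews at months 3 and 12. Cost questionnaires on healthcare use run every three months. The article condenses a fuller protocol, and the forms are not shown. The capture rates are invented, and ES several times a week gives recurrent reactions many chances to be mentioned.

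Much of this stands. Recurrence would raise capture, so the low-capture rows above are towards the pessimistic end. The ES-arm channels may pick up some reactions, which works against under-recording even as it makes contact unequal. It is also fair that the article does not say the participant alone decides on a pause, or that staff see participants only at the measurements.

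Two parts do not stand. The article is not silent on ascertainment: it states a passive method, and how adverse events are collected belongs in the protocol. And the process evaluation and cost questionnaires are not described as adverse event ascertainment, so they do not replace a common question.

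A reader might go further and infer that ES harms will be under-counted by a known amount, or that the ES arm will show an excess. The documents support neither. Passive capture lowers counts, extra contact raises them in one arm, and nothing shows which prevails.

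**Conclusion.** The point holds as a cheap improvement to safety capture, not as a contradiction or a flaw in the primary analysis. The stated method is poorly matched to a home-applied treatment with mostly transient expected reactions, and non-skin events are likely to be under-recorded. For events possible in both arms, recorded counts may not be comparable.

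This rests on two readings of the article: that the fortnightly form asks only what is described, and that no other adverse event form is in use. If the full protocol has a structured question in both arms, the point falls away. No size can be attached; the figures above show only that moderate under-capture could plausibly leave a 5% to 10% risk with no recorded case among 50 participants.

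**What to change.** Amend the section on adverse event reporting ({22}) as follows:

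1. Keep spontaneous and observed reports. Add to the existing fortnightly online questionnaire a short yes/no checklist of the symptoms listed in {11b}, phrased without reference to stimulation and worded identically in both arms.
2. In the ES arm only, add whether ES was paused or stopped since the last form, and why. This would also help explain low use in the planned adherence and dose-response work.
3. Route positive answers to the unblinded local researcher. The blinded wound-care nurse and the blinded measurement assessors should not see them.
4. Report solicited events by arm, and list spontaneous and diary-reported events separately.

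This changes data capture only and leaves the rules for pausing or stopping ES as they are.

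The cost is a small amendment and a few items in a form already sent about 26 times per participant (52 weeks / 2). Assume about a minute more each time, and more minor events to log. The same form collects the primary outcome, so the list should be short and placed after the PU question to protect completion. Participants know their allocation and may answer a symptom list differently by arm. That should be acknowledged whenever the arms are compared.

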### Frequency and plans for auditing trial conduct {23}

Once a year, the project group must submit a progress report to the Ethics Committee of Amsterdam UMC location VU and the funding agency (ZonMw). Auditing is the responsibility of the Ethics Committee who is allowed to randomly check WMO (Wet Medische-wetenschappelijk Onderzoek met mensen, i.e. Medical Research Involving Human Subjects Act) studies, however, this is not anticipated. If this trial is selected for an audit and omissions come to light, they are reported back to the principal investigator. A separate protocol and rules will be made to conform to the guidelines from the institute.

### Plans for communicating important protocol amendments to relevant parties (e.g. trial participants, ethical committees) {25}

All substantial amendments or important changes on the protocol will be indicated to the participating rehabilitation centres, sponsor and if needed to the METC and to the competent authority.

Non-substantial amendments will not be notified to the accredited METC and the competent authority, but will be recorded and filed by the sponsor. In addition, the journal, where the protocol paper and future articles were/will be published, will also be contacted.

### Dissemination plans {31a}

Implementation activities entail: understandable dissemination of results via rehabilitation specialists newsletters, patient information brochures and social media, presenting results at (inter-)national conferences, publication in high-impact peer-reviewed international journals and in Dwarslaesie Magazine (journal of the Dutch SCI patient organization) and the Nederlands Tijdschrift voor Revalidatiegeneeskunde (Dutch journal for rehabilitation medicine), and cost-effectiveness and potential scenarios for reimbursement discussions with health insurers. The participants are informed that after the research ends the sites Toetsingonline.nl and trialregister.nl will provide a summary of the results due to the registration of the study. Scientific publication or presentation by the Rehabilitation Center/Local Researcher, in whatever form, of the results of the study, will take place in accordance with the Protocol (publication agreements) and the indicated rules. All publications of the study will be coordinated by the Principal Investigator. The main researchers have the first right to publish the results of the project in scientific journals, dissertations from other academic media and will always consult the involved rehabilitation centre and/or the local investigator about a proposed publication. The final results will be submitted to a peer-reviewed scientific journal within the first year after completing the trial.

## Discussion

The aim is to conduct this study in all eight Dutch rehabilitation centres with a specialized SCI unit with motivated rehabilitation specialized and to recruit individuals with a SCI throughout the Netherlands. In addition to the complexity of setting up a good research infrastructure, this will be the first study in the field of ES for PU prevention with this relatively large number of participants (*N* = 100).

This trial will provide information about the (cost-)effectiveness of daily ES to prevent recurrent PUs and the influence of ES on the PU risk factors compared to usual care. This information is important because PUs are still a major problem within individuals with a SCI. The mechanisms by which ES can improve PU risk factors and daily living also need to be better understood. In this study, the control intervention is usual care (standard care) in the home situation, which will not be controlled in any way to make the study results as generalizable to daily practice as possible so that the effect of adding ES of the hamstrings and gluteal muscle can be identified in a real-world setting. If this study shows a positive effect, it could lead to a wide implementation of electrical stimulation in both rehabilitation centres and in people's home rehabilitation process. That is why the researchers have chosen to perform a problem analysis study to implement the results as well as possible, taking into account barriers and facilitators

## Trial status

The study is expected to be open to enrolment and start active recruiting in May 2021 with the anticipated completion date of June 2023. The total duration of the study is from May 2021 till June 2023. The trial is registered in: NTR, ID: NL9469, Protocol version 2.5 dated 20-04-2021.

## Abbreviations

PU(s): Pressure ulcer(s)
SCI: Spinal cord injury
ES: Electrical stimulation
DON: Dwarslaesie Organisatie Nederland
FSS: Fatigue Severity Scale
HADS: Hospital Anxiety and Depression Scale
PASIPD: Physical Activity Scale for Individuals with Physical Disabilities
PSQI: Pittsburgh Sleep Quality Index
SIP-68: 68-item Sickness Impact Profile
USER-P: Utrecht Scale for Evaluation of Rehabilitation-Participation (USER-participation)
WHOQOL-5: World Health Organization Quality of Life-5
(S)AE: (Serious) adverse event
METC: Medical research ethics committee (MREC); in Dutch: medisch-ethische toetsingscommissie (METc)
WMO: Medical Research Involving Human Subjects Act; in Dutch: Wet Medisch-wetenschappelijk Onderzoek met Mensen
